# Effectiveness of a three-component intervention supporting unemployed individuals with mental health issues in their job search and mental health recovery (3for1): study protocol of a non-randomized controlled study

**DOI:** 10.1186/s12889-024-20323-0

**Published:** 2024-11-14

**Keywords:** Mental health, Psychological distress, Vocational rehabilitation, Labor market integration, Unemployment, Individualized Placement and Support, Supported employment, Peer support, Peer navigator, Intervention

## Abstract

**Background:**

There is a vicious cycle between unemployment and mental health issues. Unemployed individuals with mental health issues require individualized support at multiple levels in order to promote their mental health, and obtain and retain employment. The 3for1-intervention program aims to provide such support with three components (short-term psychotherapy, job coaching based on the Individual Placement and Support approach, and peer support). This study protocol outlines how the effectiveness of this three-component intervention program in terms of re-employment, mental health, and psychosocial outcomes will be evaluated.

**Methods:**

The 3for1-intervention program will be evaluated with a non-randomized controlled trial design in a multi-center study. 500 eligible participants aged between 18 and 60 years from six job centers in Southern Germany will be allocated to a control group or an intervention group. Allocation is time-based, with the control group being recruited first, followed by recruitment of the intervention group. The control group will receive treatment as usual, whereas the intervention group will receive treatment as usual as well as access to the three intervention components over a period of 12 months. Assessment will be conducted at baseline (t0), and 12 (t1) and 18 (t3) months later. The primary outcome will be the proportion of participants who are in employment subject to social insurance contributions at t1. Differences between control and intervention group will be tested with logistic regression analysis, controlling for relevant covariates. Analyses of secondary outcomes will relate to group differences regarding re-employment, health and well-being, social integration, help-seeking, and self-stigma at t1 and t2, applying logistic regression analysis or analysis of covariance. Additionally, usage of health services will be measured to evaluate the intervention program’s cost effectiveness.

**Discussion:**

The 3for1-intervention aims to improve employability and mental health outcomes of a vulnerable population with high need for assistance. Improvements for this population would benefit the German welfare state as well. This study could provide valuable insights into the feasibility, implementation, and sustainability of this individualized, multi-level support program within German job centers.

**Trial registration:**

This trial is registered with the German Clinical Trials Register: DRKS00029002 (registered on 11 May 2022).

**Supplementary Information:**

The online version contains supplementary material available at 10.1186/s12889-024-20323-0.

## Background

Unemployment and mental health are inextricably linked in a reciprocal relationship: Being unemployed is associated with poor mental health [1–3], as well as with a higher prevalence of poor physical health and sick days [1, 4, 5], a higher rate of all-cause mortality in general [4, 6] and suicide mortality in particular [7–9]. Individuals with mental health issues, in turn, are more likely to be unemployed [2, 3, 10] and struggle to obtain and retain employment in the primary labor market [11], with increasingly poor mental health as a result. Accordingly, unemployed individuals with mental health issues can find themselves in a self-perpetuating detrimental spiral.

Employment provides many benefits to individuals, such as financial security, a purpose and role in society, social interactions, status, opportunities for personal growth, and temporal structure [12, 13]. Consequently, (re-)employment has been associated with higher self-esteem and better mental health [11, 14, 15]. Accordingly, many unemployed individuals show a high level of commitment to employment and are motivated to obtain employment [16, 17], which applies to unemployed individuals with mental health issues just the same [18–20]. However, unemployed individuals with mental health issues face multiple impediments to obtaining and retaining employment: They frequently display low levels of self-esteem and various fears about returning to work [2, 17, 19], experience stigmatization due to their unemployment as well as due to their mental health issues [19, 21, 22], and are likely to perceive low self-efficacy to obtain employment [22]. Additionally, unemployed individuals with mental health issues commonly face barriers to seeking help from mental health professionals as well, such as low mental health literacy, stigmatization, or unclear options of and pathways to appropriate treatment [23]. Consequently, they cannot benefitting from available therapies in terms of their mental health [24] that, in turn, could facilitate re-employment [25, 26].

Employment is not only beneficial for individuals’ mental health, but also highly relevant to social welfare states: In Germany, for instance, costs for unemployment amounted to €60.6 billion in 2022, which includes approximately €33.5 billion for funds spent on unemployment insurance and benefits as well as about €27.1 billion for loss of revenue due to lost social insurance contributions and lost income tax revenue [27]. Based on Germany’s Second Book of the Social Code, employment services for unemployed individuals on basic income support (i.e., *Bürgergeld*) are provided by so-called job centers. There, employment advisors are tasked with helping unemployed individuals finding re-employment and reducing barriers to employment. It is estimated that over a third of recipients of basic income support in Germany have a diagnosed mental illness, with an even higher estimated number of cases of individuals who would qualify for a diagnosis of mental illness, but lack formal diagnosis, as well as individuals whose mental health issues do not (yet) amount to a formal diagnosis, but already impede functioning [28]. For these individuals, employment advisors have various ways of supporting re-employment and health such as individual coaching, psychosocial consultation, vocational rehabilitation programs, or financial incentives for employers to enable workplace inclusion. However, it appears that the integration rate of individuals with mental health issues in the primary labor market, that is, in competitive employment, remains low [29]. On the other hand, the proportion of individuals with psychological disabilities who work in sheltered workshops steadily rising [30, 31]. Especially after having worked in sheltered workshops, (re)integration rates into the primary labor market are low [32].

One possible reason for the limited integration of individuals with mental health issues in the primary labor market could be a certain level of apprehension on the part of employers. They frequently exhibit bias against job applicants with mental health issues, perceiving them as less attractive candidates and being less likely to hire them [21, 33, 34]. This may be due to the stigma attached to individuals with mental health issues in general, as well as their presumed reliability and needs in a work-related context [35]. Regarding the latter, when experiencing episodes of more severe mental health issues, work performance can be reduced [36–38] and short-term or more long-term sick leave might be necessary [5, 38]. Furthermore, some of these individuals might have certain restrictions in terms of work tasks they can fulfill as well as how, where, and for how long they can work, thus require certain accommodations at work [19, 39, 40]. However, providing reasonable accommodations for this group of individuals has been associated with low costs, received very positively by employees, and reported to be economically beneficial for employers [39, 41]. Consequently, given the relatively high prevalence of mental health issues in the general population [42–44], which makes the employment of individuals with mental health issues no isolated cases but rather likely, and the shortage of skilled workers in Germany, employers should be willing to and will likely benefit in the long-term from employing these individuals and provide reasonable accommodations to support them in contributing to the organization, the economy, and society.

Another possible reason for the limited integration of individuals with mental health issues in the primary labor market is a certain disjointedness of social services in the German social security system: While the Federal Employment Agency and the associated job centers have a mandate to promote employability and reintegration into the labor market, the health care system is responsible for restoring and maintaining physical and mental health, and if individuals are recognized as unfit for work, they are administered by the German Pension Insurance. However, many cases have complex, overlapping requirements and need support from multiple services. Collaboration between these services can be impeded as each service is regulated by different parts of the German Social Code. This results in a “jungle” of services and bureaucracy that unemployed individuals with mental health issues as well as employment advisors in the job centers can struggle to navigate, delaying suitable support [19, 28]. In response to the low rates of inclusion into the primary labor market of individuals with complex health-related barriers, the German Federal Ministry of Labor and Social Affairs has initiated a federal funding scheme, called *rehapro*, supporting the implementation of innovative proposals for better vocational inclusion and rehabilitation of these individuals at job centers and pension insurance institutions. An important feature of this funding scheme is that the funded projects have to be evaluated scientifically.

Various intervention programs that aim to facilitate re-employment and improve mental health of unemployed individuals have been developed and evaluated, with some of these specifically focusing on individuals with mental health issues or severe mental illness. Based on systematic reviews and meta-analyses, there is consistent evidence that intervention programs which focus on mental health promotion do improve participants’ mental health [45–48]. Furthermore, some of these intervention programs have been found to have beneficial effects on participants’ re-employment, but effects were small and less consistent [46, 49]. Vocational intervention programs which focus on job placement and job skills, on the other hand, have been found to increase participants’ probability of obtaining and retaining employment, but, again, effects were small and not consistent across studies [50, 51]. More consistent and positive evidence regarding employment has been found for vocational intervention programs which specifically address employment for individuals with severe mental illness through supported employment [52–54]. Furthermore, some of these vocational intervention programs have found small, but beneficial effects for participants’ mental health [45–47]. The most beneficial and consistent effects appear to result from intervention programs which combine elements that address re-employment and mental health [45, 49].

While there have been commendable intervention programs aimed at supporting re-employment and mental health for unemployed individuals, effects on obtaining and retaining employment for those with mental health issues were low and inconsistent. This may partially be attributed to factors such as intervention program’s setting, duration, or training elements used. Firstly, many of the intervention programs have been conducted in group settings, which can provide social interaction and support, but can lack individualized support. Secondly, many intervention programs have consisted of a set of training sessions over a short amount of time, rather than long-term support. Finally, most intervention programs have focused predominantly on mental health *or* re-employment and, accordingly, employing mostly training elements that address their respective focus [46]. Consequently, participants in these programs have not benefitted from combining multiple training elements.

Given that unemployment and mental health are inextricably linked, we argue that a multi-level approach over a longer time period is necessary to provide individuals with mental health issues with more individualized support in obtaining and retaining employment as well as in their mental health recovery. Consequently, and in response to the funding call of the German Federal Ministry of Labor and Social Affairs, the research project *3for1 – Drei Wege*,* ein Ziel (Three ways*,* one goal)* was proposed.

## Objectives

The 3for1-project aims to evaluate the effectiveness of a three-component intervention program, which is conducted in collaboration with six job centers in Southern Germany. The target population consists of job center clients who receive basic income support based on Germany’s Second Book of the Social Code and who experience at least moderate psychological distress. The overall goal of the intervention program is to support the target population in obtaining and retaining competitive employment in the primary labor market subject to social insurance contributions as well as to support their mental health recovery. The three components, that is, the three ways, contribute to this goal by supporting individuals on multiple levels that focus on different areas of life. Although the components have different foci, they overlap to certain extents and work jointly toward the project’s overall goal. The first component is short-term psychotherapy which is offered on a low-threshold basis and encompasses up to ten individual sessions with a psychotherapist or psychologist with clinical training. The first component focuses predominantly on mental health recovery or placement in longer-term psychiatric or psychotherapeutic treatment. The second component is job coaching based on the Individual Placement and Support (IPS) approach which supports individuals with mental health issues in obtaining and retaining competitive employment with a good personal fit [55]; the main focus here is on reintegration into the primary labor market. The final component is peer support by peer navigators. Peer navigators are individuals with lived experience of mental health issues and life crises [56]. They focus on recovery as a process and empowering individuals in their daily life to help themselves and to take control over their situation [57]. The different components can be combined in line with the clients’ needs and wishes.

We will test the hypothesis that intervention participation as a whole improves the probability of being in employment subject to social insurance contributions 12 months after study entry in comparison to a group of the same population that receives treatment as usual (TAU) within the German social security system. Furthermore, we will test the effectiveness of intervention participation in terms of secondary outcomes that relate to (re-)employment, health and well-being, social integration, help-seeking intentions and behaviors, self-stigma, and utilization of health services within the health care system. Overall, we will test whether intervention participation is associated with more favorable outcomes than non-participation. More specifically, the following nine hypotheses are proposed:

*Hypothesis 1:* Twelve months after study entry (t1), participants in the intervention group will be significantly more likely to be in employment subject to social insurance contributions than participants in the control group.*Hypothesis 2: *Twelve months after study entry (t1), participants in the intervention group will have been significantly more days in employment subject to social insurance contributions than participants in the control group (H2a). For those that will have started such employment within 12 months after study entry (t1), the number of days until starting the first employment contract subject to social insurance contributions after study entry is significantly lower in the intervention group than in the control group (H2b).*Hypothesis 3:* Eighteen months after study entry (t2), participants in the intervention group will be significantly more likely to be in employment subject to social insurance contributions than participants in the control group.*Hypothesis 4: *Twenty-four months after study entry, participants in the intervention group will be significantly less likely to having been transferred to long-term basic income support than participants in the control group (long-term basic income support
= at least 21 months in basic income support within the preceding 24 months).*Hypothesis 5: *Twelve months after study entry (t1), participants in the intervention group will report significantly higher levels of job-search self-efficacy than participants in the control group.*Hypothesis 6: *Twelve months after study entry (t1), participants in the intervention group will report significantly more favorable outcomes on various psychosocial measures (i.e., psychological distress, health-related quality of life, general health state, somatic symptom burden, depressive symptoms, symptoms of anxiety, social integration, self-stigma) in comparison to participants in the control group.*Hypothesis 7: *Twelve months after study entry (t1), participants in the intervention group will report significantly higher intentions to and past acts of seeking professional help for mental health issues than participants in the control group.*Hypothesis 8: *Eighteen months after study entry (t2), participants in the intervention group will report significantly more favorable outcomes on the secondary outcomes mentioned in Hypotheses 5-7 than participants in the control group.*Hypothesis 9: *Of those job center clients that complete the screening measure for psychological distress, at least 30% will report experiencing at least moderate psychological distress indicated by a score of nine or greater on Kessler’s Psychological Distress Scale – K6 version [58].^1^

Furthermore, to evaluate the feasibility, implementation, and sustainability of the intervention components as regular service in job centers, we will conduct qualitative interviews with relevant stakeholders (e.g., job center executive board members, employment advisors, intervention providers, and intervention participants). Finally, we will evaluate the cost effectiveness of the 3for1-intervention program.

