### Sample size

We aim to recruit 500 participants, 250 participants per group. Sample size calculation is based on the primary outcome measure at t1 (i.e., employment status 12 months after study entry). Based on a previous longitudinal observational study with unemployed individuals with mental health issues [61], we assume a re-employment rate of 15% with TAU. We aim to achieve a re-employment rate of 30% in the IG. We conducted an a-priori power calculation for this expected intervention effect [62]: Applying a two-sided significance level of α = 0.05 and a statistical power of 0.90, we estimated that *n* = 161 participants in each group are required to show this effect. Based on previous research projects in this subject area, we anticipate a dropout rate of 35% between t0 and t1. To test the intervention effect for the primary outcome, we accordingly require an initial sample size of at least *n* = 248 participants per group at t0.

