### Statistical methods

For the analysis of the primary outcome, logistic regression analysis will be applied. Logistic regression analysis enables the prediction of the binary outcome (in employment: yes vs. no) based on the binary group status (CG vs. IG), while controlling for relevant covariates such as the job center that the participant is registered with, the unemployment rate of the respective districts, duration of unemployment and of receiving basic income support, as well as baseline demographic variables which are significantly different in the two groups. The secondary outcomes will be analyzed with varied analysis methods based on the characteristics of the data: For the hypotheses which propose differences in binary outcomes (i.e., Hypotheses 3–4), logistic regression analysis will be applied; for hypotheses that predict difference in continuous outcomes (i.e., Hypotheses 2, 5–8), we will apply analyses of covariance to compare the two study groups. To estimate the prevalence of increased psychological distress in job center clients that complete the screening measure, we will conduct a frequency analysis (i.e., Hypothesis 9).

Additionally, we will analyze the cost-effectiveness of the intervention from two perspectives: We will address the intervention’s cost effectiveness in terms of benefits of employment for the social welfare state. More specifically, we will balance the costs for the intervention with the reduced costs for basic income support and related social welfare benefits. Furthermore, we will evaluate the intervention’s cost-effectiveness by relating the incremental total costs of illness, including the direct costs of health service utilization and the indirect costs of productivity loss, to the incremental gain in quality adjusted life years (QALYs) [97, 98].

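### H2b compares days to first job only among participants who found one, so it does not measure whether 3for1 shortens time to employment

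*Protocol article*

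**What the plan says.** The Objectives section splits Hypothesis 2 in two. H2a compares days in insured employment over 12 months and carries no restriction on who is analysed. H2b is restricted: "For those that will have started such employment within 12 months after study entry (t1), the number of days until starting" the first insured contract "after study entry is significantly lower in the intervention group than in the control group (H2b").

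The Statistical methods section fixes the technique for Hypothesis 2 as a whole: "for hypotheses that predict difference in continuous outcomes (i.e., Hypotheses 2, 5–8), we will apply analyses of covariance to compare the two study groups". The article names no time-to-event method and no censoring for H2b, and it does not address selection into the starter subset.

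The Sample size section gives the planned effect on employment status at 12 months: "we assume a re-employment rate of 15% with TAU" and "We aim to achieve a re-employment rate of 30% in the IG". Under Secondary outcomes, start and end dates of jobs are to be asked for in the exit (t1) and follow-up (t2) interviews.

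**The concern.** H2b asks a time-to-event question but answers it in a subset defined by the event. Whether a participant starts a job within 12 months is decided after allocation, and raising that proportion is the purpose of the programme. If the planned doubling is achieved by adding starters, about half of those in the intervention group (IG) would not have started under usual care and have no counterpart among control group (CG) starters. Adjusting for baseline covariates does not remove selection on a post-entry event. This selection comes on top of the non-randomized allocation that the Discussion already concedes.

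Participants still without a job at 12 months are left out, although the fact that they waited the whole year without a start is information on speed. At stake is the reading of a directional hypothesis: a programme that places more people could be reported as not speeding up re-employment, or as slowing it. Because subset and method are both stated, this is not a detail left to a later analysis plan.

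**Working it through.** **The plan's own figure first.** Inputs from Sample size: 15% vs 30%, with test settings "Applying a two-sided significance level of α = 0.05 and a statistical power of 0.90". With pooled variance and mean proportion 0.225:

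n = [1.960·√(2·0.225·0.775) + 1.282·√(0.15·0.85 + 0.30·0.70)]² / 0.15² = 160.8, so 161.

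This reproduces "161 participants in each group are required to show this effect". Inflating for 35% dropout gives 161/0.65 = 247.7, so 248, as stated. The article gives no power figure for H2b.

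**Assumptions added here.** (a) The 15% and 30% are rates of being employed at t1; they stand in for ever having started a job within 12 months. (b) The timing of starts is not in the article, so three patterns are tried. (c) A t-test stands in for the analysis of covariance. Covariates could reduce the residual SD somewhat but would not change what is compared.

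**Pattern 1: constant hazards.**
- Yearly hazards: −ln(0.85) = 0.1625 (CG) and −ln(0.70) = 0.3567 (IG); hazard ratio 2.19.
- Mean days among starters = 1/λ − 365·(1−p)/p, with λ per day. CG: 2245.9 − 2068.3 = 177.6. IG: 1023.3 − 851.7 = 171.7 (from unrounded terms). Difference 5.9 days; SD about 105 in each group.
- Expected starters: 161·0.15 = 24.2 and 161·0.30 = 48.3.
- Standard error = √(105.3²/24.15 + 105.0²/48.3) = 26.2 days; difference/SE = 0.224.
- Two-sided power = Φ(0.224 − 1.96) + Φ(−0.224 − 1.96) = 0.041 + 0.014 = 0.056. In 5,000 simulated trials about 4% were significant in favour of the IG, and the sign was wrong in 42%.
- Smallest difference detectable with 80% power: (1.96 + 0.842)·26.2 = about 73 days.
- Log-rank on everyone: Φ(ln 2.195·√72.45/2 − 1.96) = Φ(3.345 − 1.96) = 0.92; simulated 0.91.
- With all 250 per group, power for H2b is still only 0.059.
- If more people ever start a job than are employed at t1 (20/40%, 25/45% or 30/50%), power for H2b is 0.07 to 0.10.

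**Patterns 2 and 3: 15% start uniformly over the year in both groups, and a further 15% start in the IG.**
- Extra starts in months 4-12: CG mean 182.5; extra starters' mean (121.7 + 365)/2 = 243.3; IG mean (182.5 + 243.3)/2 = 212.9, so the IG looks about 30 days slower (31 in simulation).
- Extra starts in months 0-6: extra starters' mean 91.25; IG mean (182.5 + 91.25)/2 = 136.9, so the IG looks about 45 days faster.

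| Timing of extra IG starts (161 per group) | IG − CG among starters | H2b significant for IG | H2b wrong sign | H2b significantly wrong | Log-rank on all, for IG |
|---|---|---|---|---|---|
| Constant hazards | −6 days | about 0.04 | 42% | about 2% | 0.91 |
| Months 4-12 | +31 days | below 0.01 | 88% | about 24% | 0.89 |
| Months 0-6 | −45 days | about 0.44 | 4% | 0% | 0.92 |

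In all three patterns the programme doubles placement. The analysis of everyone shows this each time, while H2b changes sign with the timing.

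**The case against.** Four points on the other side have weight.

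*H2a covers part of the question.* It is not restricted to starters. If a job once started is kept, days employed equals 365 minus the start day, and 0 for non-starters, which is close to a restricted mean time measure. Under constant hazards with jobs kept, H2a has power of about 0.82. A reader might infer that the trial would be left unable to show any effect on employment timing; the article does not support that. H2a does mix speed with job retention, so its coverage is partial.

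*Low power is not universal.* A reader might infer that H2b has almost no power whatever happens, or that it usually points the wrong way. Both depend on timing that the article does not give. The Job coaching section describes an aim of relatively rapid placement, so early gains are plausible, and with extra starts in months 0-6 the sign is right and power is about 0.44. Even so, this is about half the power of the log-rank test, and the contrast still mixes speed with who was placed.

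*Harder-to-place starters are an assumption.* It is tempting to say that the IG subset adds people who are harder to place. Nothing in the article shows it, and the calculations above do not need it.

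*The subset is openly labelled and H2b is secondary.* Both are true. The primary outcome, its sample size, H1, H2a, H3 and H4 do not depend on H2b. This limits the severity; it does not make the starter subsets comparable.

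**Conclusion.** The point stands: H2b, as worded and assigned to analysis of covariance, conditions on a post-allocation outcome that the programme is meant to change, and so does not measure whether 3for1 shortens time to employment. That conclusion needs no assumption about timing. The size does. With 15%/30% as a proxy for ever having started and 161 analysed per group, results range from about 31 days slower (significantly wrong in about 24% of trials), through a 6-day difference with about 5% power, to about 45 days faster with power about 0.44. The log-rank test on everyone stays at about 0.89 to 0.92 throughout.

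This should be fixed, but it is not a defect that puts the trial's main conclusion at risk.

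**What to change.** Redefine H2b as time from study entry to first insured employment in all participants with employment data from the t1 (or t2) interview, with non-starters censored at 12 months. Analyse it by Kaplan-Meier curves and Cox or discrete-time regression with the covariates already planned. Report days to start among starters as a descriptive figure only.

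This cannot simply mean everyone allocated. Employment dates come only from the t1 and t2 interviews, the six-month contact covers health service use, and 35% dropout by t1 is expected. Participants with no employment follow-up should be handled as for the primary outcome. For anyone who missed t1, the t2 interview should ask about jobs back to study entry.

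The cost is wording in the hypothesis and the statistical methods, plus the matching update to the registration. No new data item is needed, because start dates are already collected. The change should be made before t1 outcomes are analysed; the article expects t1 to be complete in June 2025.
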